#### Primary outcome

NRS is a commonly used scale for assessing clinical pain. It is easier for patients to grade pain intensity with numbers rather than other measurements like the visual analog scale. The NRS is an 11-point scale for pain, with 0 indicating no pain and 10 indicating the worst possible pain. NRS pain scores will be assessed hourly for 6 h after surgery, then daily for 3 days [21, 22].

#### Heart rate and blood pressure

HR and BP will be monitored during and after the operation. These vital signs have been extensively utilized and validated. HR and BP will be assessed hourly for 6 h after surgery, then daily for 3 days.

#### Sleep quality

An actigraph device measures sleep quality when worn on the wrist overnight. The main sleep indexes are sleep efficiency, total sleep time, and sleep awakenings. Sleep condition and sleep quality will be analyzed using the software ActiLife6 (Version 6.8.1, Actigraph LLC) [23]. Sleep quality will be assessed five times: the night before the operation, the night after the operation, and three subsequent nights until discharge.

#### Quality of recovery

The 15-item Quality of Recovery Scale (QoR-15) is a valid, extensive, and efficient evaluation of a patient’s postoperative recovery. The QoR-15 measures five aspects of recovery: pain, physical comfort, physical independence, psychological support, and emotional state. The questionnaire consists of 15 items with a score from 0 to 10, with 0 representing no pain and 10 representing pain always present. The sum of the scores is the patient’s QoR-15 score [24]. QoR-15 will be assessed twice: after surgery and on the day of discharge.

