### Sample size

This is a pilot study. In the relevant literature, there are no previous studies utilizing the same evaluation method as the primary outcome to compare a sham acupuncture control. Therefore, we were unable to calculate the statistical power formally. The appropriate sample size for a two-arm pilot study should be more than 12. We assumed a 20% dropout rate, so that we will recruit 15 participants into each group. We will, therefore, recruit a total of 30 individuals for this RCT [13–15].

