### Intervention protocol

All participants will be asked to fast from 8 h before the operation. They will undergo a standard operative procedure and receive postoperative treatment. Participants will be transferred to the ward within 30 min after the operation. EA or SEA will be given within 2 h prior to the surgery, immediately after surgery on arrival in the recovery ward, and daily following surgery for 3 days (five treatment sessions in total). If a participant drops out before completing the study, the reason will be recorded.

The acupuncture methods are described in Table 2. In each treatment session, the patients will be in a private area and placed in the supine position. They will wear an eye mask to prevent them from observing the treatment procedure. The researcher will sterilize the patient’s skin with 75% alcohol wipes before treatment. Each treatment session will last for 30 min. When the needles are removed, the researcher will use a clean piece of cotton wool to prevent bleeding by compressing the points. In the first treatment, 11 acupoints will be used and 17 acupoints will be used in the subsequent postoperative treatments. The acupoints and rationale are summarized in Table 3.

**Table 2 Tab2:** Treatment methods of electroacupuncture and acupoints

	EA group	SEA group
Acupoints	All sessions: LI4, PC6, HT7, LI20, ST36, GV23 Postoperatively: GV20, GV29, EX-HN22, SP6	All sessions: LI4, PC6, HT7, LI20, ST36, GV23 Postoperatively: GV20, GV29, EX-HN22, SP6
Depth of insertion	10 mm: HT7, GV20, GV23, GV29, LI4, LR3	No insertion
	30 mm: LI20, SP6, PC6, ST36	
Needle type	Steel needles (Wuxi Jiajian Medical Co. Ltd. Wuxi, China)	Blunt needles (Streitberger placebo needle)
Needle sensation	With *de-qi* sensation	Without *de-qi* sensation
Electric stimulation	Three pairs of needles: LI4–ST36 (bilaterally), GV20–GV23 Connected to an electric stimulator (HANS-200B) Deliver continuous wave-type mid-frequency (15Hz) current of 2 mA	Three pairs of needles: LI4–ST36 (bilaterally), GV20–GV23 Connected to an electric stimulator (HANS-200B) No electrical current delivered

*EA* electroacupuncture, *SEA* sham electroacupuncture

**Table 3 Tab3:** Acupoint selection and rationale based on traditional Chinese medicine

Acupoint	Location	Traditional Chinese medicine indication	Suggested technique

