#### Overall health

The 36-item Short Form Health Survey (SF-36) consists of 36 items in eight multi-item scales (physical functioning, physical role, bodily pain, general health, vitality, social functioning, emotional role, and mental health) and one single-item scale (health transition). Higher scores represent better health status [25]. SF-36 will be assessed twice: after surgery and on the day of discharge.

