### Statistical analysis

An independent statistician blinded to group allocation will perform the statistical analyses using the statistical software SPSS 23.0 for Windows. The analyses will include an intention-to-treat analysis incorporating data from any participants who have dropped out of the trial. We will use multiple imputation for missing data. All demographic and clinical characteristics of the subjects (such as sex, age, and weight) will be analyzed using descriptive statistics. We will identify the homogeneity of demographic characteristics and study variables between the two groups. Continuous variables will be reported as means ± standard deviations whereas qualitative data will be presented as frequencies and percentages. To analyze the primary outcome, the area under the curve of the NRS pain scores will be calculated using the trapezoidal method. Comparisons between groups will be made using Student’s *t*-test. The secondary outcomes—BP, HR, QoR-15, SF-36, and actigraphy assessments (total sleep time, sleep awakenings, and sleep efficiency)—will be compared between the two groups with Student’s *t*-test or the Wilcoxon rank-sum test. All reported *p* values will be two-sided, and *p* < 0.05 is considered statistically significant.

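### Sleep and HR/BP are compared with unadjusted tests although baselines are collected, and QoR-15 and SF-36 have no pre-treatment value to adjust for

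*Protocol article*

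**What the plan says.** All references are to the protocol article.

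- **Start of treatment** (Intervention protocol): "EA or SEA will be given within 2 h prior to the surgery, immediately after surgery on arrival in the recovery ward". The first session therefore precedes the operation.
- **QoR-15** (Quality of recovery): "QoR-15 will be assessed twice: after surgery and on the day of discharge".
- **SF-36** (Overall health): "SF-36 will be assessed twice: after surgery and on the day of discharge". Table 1 agrees for both scales: marks at recovery and on the day of discharge, none under screening or baseline.
- **Sleep** (Sleep quality): "Sleep quality will be assessed five times: the night before the operation, the night after the operation", followed by three further nights. The first of these nights precedes any treatment.
- **HR and BP** (Table 1): vital signs are marked at screening and at baseline, and the Safety assessment section counts HR and BP among the vital signs.
- **Analysis** (Statistical analysis): BP, HR, QoR-15, SF-36 and the three actigraphy indices "will be compared between the two groups with Student’s *t*-test or the Wilcoxon rank-sum test". No covariate is named. The only stated use of baseline data is descriptive, together with a check that the groups are alike on demographics and study variables.

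**The concern.** There are two separate weaknesses.

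First, for sleep and HR/BP the trial will already hold a pre-treatment measurement of the same quantity in each patient, and the named tests do not use it. Checking the groups for similarity corrects nothing. If the groups differ at baseline, the check shows the problem and the planned test leaves it in the estimate.

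Second, for QoR-15 and SF-36 there is nothing to check or adjust for, because the first value comes after the first session and the operation. A later analysis plan can add covariates, but it cannot supply a measurement that was never taken.

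With 15 patients per arm, chance differences at baseline can be sizeable. The trial is also a pilot meant to inform a full-scale study. Without pre-treatment values it cannot estimate the baseline-outcome correlation for QoR-15 and SF-36, which is needed to size a baseline-adjusted main trial.

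**Working it through.** **Inputs.** The Sample size section gives "The appropriate sample size for a two-arm pilot study should be more than 12" and "We assumed a 20% dropout rate, so that we will recruit 15 participants into each group". Reading the minimum as 12 per arm, 12 / (1 − 0.20) = 15 per arm, or 30 in total, which reproduces the plan's figure. The plan states no effect size, SD or power. The baseline-outcome correlation r is not given either, so r = 0.3, 0.5 and 0.7 are assumed throughout.

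**Chance imbalance.** In SD units, the between-group difference in baseline means has standard deviation √(2/n).

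- n = 15: √(2/15) = 0.365. 0.5 / 0.365 = 1.37, so P(|difference| > 0.5 SD) = 17%.
- n = 12 (after 20% dropout): √(2/12) = 0.408. 0.5 / 0.408 = 1.22, giving 22%.

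**Effect on the unadjusted estimate.** A baseline imbalance of 0.5 SD shifts the outcome difference by r × 0.5, that is 0.15, 0.25 or 0.35 SD. In a simulation of 100,000 null trials per value of r, with 15 per arm, the unadjusted t-test rejected in about 5% of all trials. Among trials with an imbalance above 0.5 SD, it rejected in about 7%, 11% or 18%.

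**Effect on precision.** Adjustment leaves a fraction 1 − r² of the residual variance. The detectable difference and the power come from the noncentral t distribution at two-sided 5% with 15 per arm. The adjusted variance is multiplied by 1 + 1/(2n − 4) = 27/26 to allow for estimating the slope.

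| | t-test | r = 0.3 | r = 0.5 | r = 0.7 |
|---|---|---|---|---|
| Residual variance, 1 − r² | 100% | 91% | 75% | 51% |
| Equivalent n per arm, 15/(1 − r²) | 15 | 16.5 | 20 | 29.4 |
| Difference detectable with 80% power (SD) | 1.06 | 1.03 | 0.94 | 0.77 |
| Power at an assumed 0.8 SD effect | 56% | 58% | 67% | 83% |

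The first two rows omit the slope cost. With it, the variance ratios are 0.91 × 27/26 = 0.945, 0.75 × 27/26 = 0.779 and 0.51 × 27/26 = 0.530. Ignoring the single degree of freedom lost, adjustment breaks even where (1 − r²) × 27/26 = 1, so r² = 1/27 and r ≈ 0.19. Below that, it gains nothing.

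**The case against.** Randomisation makes an unadjusted comparison legitimate, and this is a 30-patient pilot without a formal power calculation. That stands: the named tests are not invalid, and adjustment is an improvement in efficiency. The size of the gain also rests on an r that the article does not give. At r = 0.3, power moves only from 56% to 58%. An analysis plan that is not shown could add covariates for sleep and HR/BP. It could not supply the missing QoR-15 and SF-36 values.

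Three stronger readings are tempting, and the article does not support them.

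- **The primary outcome lacks a true baseline.** A reader might infer this because the NRS is also first scored after surgery. But the outcome is postoperative pain, which has no direct preoperative counterpart. Patients with chronic pain currently requiring an opioid or NSAID are excluded, so preoperative scores may be low and predict little. A t-test on the postoperative area under the curve is a sound analysis.
- **The recovery-ward score will serve as baseline, removing part of the treatment effect.** That would be a fault if planned, but the Statistical analysis section names no change score.
- **Each secondary outcome will be tested at every time point, producing many false positives.** The section does not say how repeated HR, BP and sleep values are summarised. Per-time-point testing is therefore an inference.

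**Conclusion.** The point holds for sleep, HR/BP, QoR-15 and SF-36. For sleep and HR/BP, the named tests leave out baselines that the trial already collects, beyond at most a homogeneity check. For QoR-15 and SF-36, the schedule rules out any pre-treatment comparison or adjustment.

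The consequence is lost precision and bias conditional on the imbalance that arises; overall type I error is not inflated. The probability of an imbalance above 0.5 SD is 17% at 15 per arm and 22% at 12. It rests on normal sampling of the baseline means and on no figure outside the plan beyond reading the pilot minimum as 12 per arm. The precision gain depends wholly on the assumed r, from almost nothing at 0.3 to roughly half the residual variance at 0.7. The correlation may differ between instruments, and nothing in the article shows which value applies to which.

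**What to change.** 1. **Sleep and HR/BP.** In the Statistical analysis section, replace the unadjusted tests with a baseline-adjusted model for each sleep index and for HR and BP. This can be ANCOVA on a per-patient postoperative summary, or a repeated-measures mixed model. Use the pre-operation night as covariate for sleep and the baseline vital signs for HR and BP. The baseline-column reading is the safer choice for HR/BP, because Table 1 does not say whether the reading within 2 h before the operation precedes the session. Report one between-group difference with 95% CI per outcome. This needs no new data, only wording.
2. **QoR-15 and SF-36.** Mark both in the baseline column of Table 1, before the first session, and analyse the discharge values by ANCOVA on that baseline. Do not use the recovery-ward value as the covariate. The cost is a protocol amendment and a short added questionnaire burden at an existing assessment. The Trial status section describes the trial as still in preparation, and the change only helps patients enrolled after it is made.
3. **NRS.** A preoperative score is optional, and its gain is probably small. The primary analysis can stay as it is.

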#### Overall health

The 36-item Short Form Health Survey (SF-36) consists of 36 items in eight multi-item scales (physical functioning, physical role, bodily pain, general health, vitality, social functioning, emotional role, and mental health) and one single-item scale (health transition). Higher scores represent better health status [25]. SF-36 will be assessed twice: after surgery and on the day of discharge.

### Safety assessment

Before signing the informed consent form, participants will be told about the potential adverse events related to acupuncture, such as bruises, hematomas, infection, and pain. Adverse events will be graded as 1 (mild), 2 (moderate), or 3 (severe or medically significant). Any adverse events that occur during the trial will be recorded by the patients and doctors. Vital signs will be assessed at the time of the event, including HR, BP, and respiratory rate. All details of adverse events will be reported in a case report form. If any severe adverse event occurs, we will terminate the EA or SEA treatment and the Clinical Research Center for Drugs of the Shanghai University of Traditional Chinese Medicine will unblind the participant to determine whether the serious adverse event is related to EA or SEA. A final decision will made on whether to continue the study. We will analyze the influence of all events at the end of the trial.

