**Methods/design:**

This randomized sham-controlled patient- and assessor-blind pilot trial has been designed to evaluate the efficacy and safety of electroacupuncture in managing postoperative pain following nasal endoscopic surgery to treat sinusitis due to nasal polyps. Altogether, 30 participants will be randomly allocated to an electroacupuncture or non-invasive sham control in a 1:1 ratio. Treatment will occur within 2 h before the operation, immediately after the operation upon arrival in the recovery ward, and once daily for 3 days. The primary outcome is the pain numerical rating scale, which will be analyzed using the area under the curve. The secondary outcome measures include heart rate and blood pressure after the operation, sleep quality during the hospital stay (actigraph), quality of recovery, and the 36-item short form health survey. This trial will use an intention-to-treat analysis.

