## Background

Postoperative pain is an important symptom following nasal endoscopic surgery for sinusitis due to nasal polyps. Effective management of postoperative pain after nasal endoscopic surgery is especially important for patient recovery. Pain due to a nasal filling may interfere with breathing, sleep quality, and patient satisfaction. According to previous reports, a failure to treat acute pain immediately may cause long-term chronic pain [1, 2]. The effective relief of acute pain is a challenge for patients and physicians following nasal endoscopy. Analgesic drugs, especially opioid analgesics, are often used to relieve pain after surgery. However, there are risks due to side effects, such as respiratory depression and drowsiness, which can lead to a delayed postoperative recovery. Thus, a safe and effective way to control postoperative pain and reduce recovery times needs to be identified.

Acupuncture has been widely used for pain relief, and its analgesic effects have been reported worldwide. Several studies have shown that acupuncture can relieve pain after surgery, including oral surgery [3, 4], cardiac surgery [5], laparoscopic cholecystectomy [6–8], gynecological surgery [9, 10], back surgery [11], and nasal surgery [12]. Therefore, acupuncture may relieve postoperative pain following nasal endoscopic surgery. Despite the positive results of these previously published studies, the results are not dependable due to issues such as small sample sizes, inadequate randomization, and lack of blinding. Therefore, high-quality evidence is needed to confirm the previous findings and for a protocol to be developed for the use of acupuncture for postoperative pain.

For those reasons, we designed a randomized controlled trial (RCT) using appropriate randomization, rigorous concealment of allocation, and blinding to examine the efficacy of electroacupuncture (EA) in relieving postoperative pain after nasal endoscopy. We aim to determine: (1) whether EA is useful for relieving postoperative pain after nasal endoscopy and (2) whether it can reduce postoperative recovery times. This study may provide high-quality evidence to support a standard protocol for the clinical application of EA for treating postoperative pain after nasal endoscopic surgery.

We hypothesize that EA is effective, safe, and feasible for postoperative pain management after nasal endoscopic surgery.

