### Recruitment

Patients will be recruited to this RCT in Shanghai Municipal Hospital of Traditional Chinese Medicine. Eligible subjects who have been scheduled for nasal endoscopic surgery for sinusitis due to nasal polyps will be invited to participate. They will be referred from an otorhinolaryngologist. A research assistant will screen them and obtain written informed consent. They will then be randomly allocated to either the EA group or the SEA group. The schedule of enrolment, intervention, and assessments is detailed in Table 1.

**Table 1 Tab1:** Schedule of enrolment, intervention, and assessments

	S	B	O	Preoperative period	Postoperative period		
Timepoint				Within 2 h before operation	Upon recovery	Hourly for 6 h after surgery	Once daily until discharge
Basic information							
Informed consent	X						
Inclusion/exclusion	X	X					
Medical history	X						
Vital signs	X	X	X	X	X	X	X
Interventions							
EA				X	X		X
Sham EA				X	X		X
Assessments							
Primary outcome							
NRS					X	X	X
Secondary outcomes							
HR and BP			X	X	X	X	X
Actigraphy		X	X				X
QoR-15					X		X^*^
SF-36					X		X^*^
Others							
Adverse events			X	X	X	X	X
Patient satisfaction							X
Success of blinding							X

*EA* electroacupuncture, *S* screening, *B* baseline, *O* operation, *NRS* numerical rating scale, *HR* heart rate, *BP* blood pressure, *QoR-15* 15-item Quality of Recovery Scale, *SF-36* 36-item Short From health survey

* On day of discharge

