### Data management

The clinical trial management platform ResMan will be used to manage the original data, which will be collected by blinded assessors and double-entered. The data management system will be tested beforehand, and relevant users will be trained on it before it is officially launched. The database will be protected by passwords. The original data for a participant will be entered within 1 week after their discharge from hospital. If there are issues with the data, the data supervisor will request clarification from a researcher. The clinical supervisor will monitor the work of the clinical trial center at least once a month.

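### The last scheduled adverse-event assessment is at discharge, 0 to 1 day after the final session, so late needle-site events, chiefly infection, are only partly captured, and the loss falls essentially on the electroacupuncture arm

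*Protocol article*

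**What the plan says.** - **Safety as an aim.** The abstract says that the trial is to "evaluate the efficacy and safety of electroacupuncture in managing postoperative pain". The Background adds: "We hypothesize that EA is effective, safe, and feasible for postoperative pain management after nasal endoscopic surgery". The Discussion says that a finding of efficacy and safety could support a new standard of care.
- **What is recorded.** Under Safety assessment, participants are told of "potential adverse events related to acupuncture, such as bruises, hematomas, infection, and pain", and "Any adverse events that occur during the trial will be recorded by the patients and doctors". No end of the recording period is given there.
- **When it is scheduled.** Outcome measures refers to Table 1 for the assessment schedule. Table 1 marks adverse events from the operation through to the column "Once daily until discharge", which is the last column.
- **When patients go home.** The Intervention protocol gives five sessions: before surgery, on arrival in the recovery ward, and on each of the next three days. Sleep is recorded on "the night before the operation, the night after the operation, and three subsequent nights until discharge".
- **Skin penetration.** The Control group section and Table 2 say that sham needles touch the skin but do not enter it.
- **Data entry.** "The original data for a participant will be entered within 1 week after their discharge from hospital".
- **Participants who leave the protocol.** Outcome measures says that data collection stops for a participant who cannot be managed as planned, and it lists side effects among the reasons.

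**The concern.** Safety is one of the trial's stated aims, and infection is one of four acupuncture-related events that the article names. Infection at a puncture site may take days to show. If the last planned look is at discharge, an infection that appears at home reaches the data only if someone happens to report it.

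The loss would not be even. The sham arm has no punctures, so missed needle-site infections belong essentially to the EA arm. The undercount favours a conclusion of safety, and the pilot is meant to inform the design of a full-scale trial, which could inherit the same short window.

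**Working it through.** **The plan's own figures.** No stated figure concerns the adverse-event window. The related figures reproduce:
- Sample size, reading the minimum of 12 as per arm: 12 / (1 − 0.20) = 15 per arm, 30 in total.
- Points per session: 11 before surgery and 11 + 6 = 17 in each of four postoperative sessions.
- Insertions per EA patient: 11 + 4 × 17 = 79. The last session contributes 17 / 79 = 21.5%.

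**Observation window.** Sessions fall on days 0, 0, 1, 2 and 3, counting surgery as day 0. The night of surgery plus three more nights puts discharge at about day 4; day 3 is taken as the lower case. Window = discharge day − session day:
- Discharge on day 4: 4, 4, 3, 2, 1 days (mean 2.8).
- Discharge on day 3: 3, 3, 2, 1, 0 days (mean 1.8).

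**Share of late events captured.** The documents give no onset time, so the onsets below are assumptions that show a range. Risk is taken as equal per session. For a window *w*, a fixed onset is captured if *w* is at least that long; a uniform onset over 2 to 7 days is captured with probability (*w* − 2)/5, limited to 0 to 1; an exponential onset with mean *m* is captured with probability 1 − exp(−*w*/*m*). Each entry is the average over the five sessions. The last column is for a contact 7 days after the last session (day 10; windows 10, 10, 9, 8, 7).

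| Assumed onset | Discharge day 3 | Discharge day 4 | Contact on day 10 |
|---|---|---|---|
| Fixed, 2 days | 3/5 = 60% | 4/5 = 80% | 100% |
| Fixed, 3 days | 2/5 = 40% | 3/5 = 60% | 100% |
| Fixed, 5 or 7 days | 0% | 0% | 100% |
| Uniform, 2 to 7 days | (0.2 + 0.2)/5 = 8% | (0.4 + 0.4 + 0.2)/5 = 20% | 100% |
| Exponential, mean 3 days | 40.7% | 57.5% | 94.2% |
| Exponential, mean 5 days | 28.3% | 41.3% | 82.3% |
| Exponential, mean 7 days | 21.6% | 32.0% | 71.1% |

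Weighting by insertions instead of sessions changes the uniform row little: 5.6/79 = 7% and 14.6/79 = 18%.

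**Last session alone.** With 0 to 1 day of observation, nothing is captured under a fixed or uniform onset of 2 days or more. Under the exponential onsets, discharge on day 4 captures between 1 − exp(−1/7) = 13% and 1 − exp(−1/3) = 28%; discharge on day 3 captures nothing.

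**Direction.** Let *p* be the true risk of needle-site infection under EA, *c* the share captured, and the sham risk essentially zero. The observed difference is *c* × *p* instead of *p*, so it is too small by (1 − *c*) × *p*. Neither *p* nor *c* is in the documents, so only the sign is known.

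**Precision.** With 15 EA patients and no events, the two-sided 95% upper limit is 1 − 0.025^(1/15) = 21.8%. A true risk of 1% would show at least one event with probability 1 − 0.99^15 = 14%, even with complete follow-up.

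**The case against.** Several stronger readings are tempting, and the documents do not support them.

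- *Delayed events cannot be captured at all.* Not so. The first two sessions have 3 to 4 days of observation, and a 2-day onset would be seen after 60% to 80% of sessions. Of the four named events, bruising, hematoma and needling pain would mostly be expected within the stay; infection is the one that is plausibly late.
- *The data are closed within a week of discharge.* The Data management section sets a deadline for entry and then describes queries. It is not a database lock, and it does not say that later reports are discarded.
- *Truncation hides events in one arm only.* That holds only for events that need a punctured skin. Both arms have the same surgery, and other late events would be missed in both.
- *The bias is known to be large.* Without an event rate or an onset time, no size can be given.

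It can also be argued that the safety sentence says only that events during the trial are recorded, that a condensed article may leave post-discharge reporting to the full protocol, and that 15 patients per arm limits any safety claim far more than a missing call does. The last point stands: the fix will not make this a safety trial. The others weaken the case without removing it. Table 1 sets a schedule that ends at discharge, and the blinding question, asked after the final treatment, tells participants that the study is over. Small numbers show up in a confidence interval; events that nobody asks about do not.

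**Conclusion.** The point holds in limited form and is worth correcting. By the published schedule, adverse events are last assessed at discharge, 0 to 1 day after the last session and at most about 4 days after the first. Late needle-site events, chiefly infection, are partly captured overall, and little or not at all after the last session, which accounts for 21.5% of insertions. Such missed events fall essentially in the EA arm and move the comparison toward no difference.

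This rests on discharge at day 3 to 4, which is inferred from the sleep schedule, and on the absence of any post-discharge contact from the article. A longer stay would lengthen the window. The captured shares of 0% to 80% depend wholly on assumed onsets and are not estimates.

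A related conflict is more direct. Stopping all data collection when side effects prevent management by protocol cannot stand beside the recording of any adverse event during the trial. Read literally, it ends the record when harm occurs.

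**What to change.** 1. In Table 1 and the Safety assessment section, add one telephone contact after discharge at a fixed time, for example about 7 days after the last session (day 10). The existing blinded assessor should make it, with identical questions in both arms, and the text should name it as the end of the adverse-event window. Because the efficacy assessments in Table 1 end at discharge, questions about needle sites cannot unblind the assessor for those outcomes.
2. If no contact is added, state that adverse-event recording ends at discharge and limit the safety conclusion explicitly to the in-hospital period.
3. Reconcile the stopping rule under Outcome measures with the Safety assessment section, so that adverse-event recording continues for participants who leave the protocol.

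The cost is about 30 short calls by existing staff, one more column in Table 1, and slightly later completion of each participant's adverse-event data. The present entry deadline falls at about day 10 to 11 (day 3 or 4 plus 7), so it needs at most a small adjustment. The sample size is unchanged.

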### Randomization and allocation concealment

A random sequence will be produced by block randomization using the software SPSS version 23.0 by an independent research assistant. After the participants have completed the screening process and baseline assessment, they will be randomly assigned to one of the groups in a 1:1 ratio using random numbers in opaque envelopes. The treatment allocation codes will not be revealed before the first treatment. In an effort to minimize breaks in coding, the principal investigator who designed the trial and the research personnel who perform the outcome assessments will also be blinded to the treatment assignment.

Before the beginning of treatment, we will tell the participants that they have the same probability of being assigned to the EA group or the SEA group. To ensure that participants remain blinded, they will wear an eye mask during treatment. Only the acupuncturist who performs the treatment will know the group allocation at the time of treatment. The principal investigator, the data analysts, the outcome assessors, and statistician will remain blinded.

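### The protocol breaks the treatment code in order to decide whether a severe or serious adverse event is related, so attribution of these few events can be influenced by the arm (minor)

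*Protocol article*

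**What the plan says.** The Safety assessment section of the protocol article grades events on three levels: "Adverse events will be graded as 1 (mild), 2 (moderate), or 3 (severe or medically significant"). Recording does not depend on cause: "Any adverse events that occur during the trial will be recorded by the patients and doctors". Details go into a case report form.

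The section then fixes a procedure for the gravest events. It opens with "If any severe adverse event occurs, we will terminate the EA or SEA treatment" and goes on, in the same sentence, to say that the Clinical Research Center "will unblind the participant to determine whether the serious adverse event is related to EA or SEA". The next sentence provides for a decision on whether the study continues. The section closes with "We will analyze the influence of all events at the end of the trial".

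Two other places bear on the point. The Abstract says the trial is "designed to evaluate the efficacy and safety of electroacupuncture in managing postoperative pain". Randomization and allocation concealment says: "The principal investigator, the data analysts, the outcome assessors, and statistician will remain blinded". That list does not mention whoever judges the cause of an adverse event.

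**The concern.** Relatedness is an opinion, and the protocol has it formed with the arm known. The arms differ in exactly what would steer that opinion: the EA arm has needles inserted and current delivered, while the sham arm has blunt needles that do not penetrate and no current (Table 2 and the two intervention sections). Infection and pain appear in the protocol's own list of possible acupuncture harms, yet either could also follow nasal surgery. An assessor told that nothing was inserted is drawn towards *unrelated*; one told that needles and current were used is drawn towards *related*. The same clinical picture can then get a different verdict in each arm.

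Two things are at stake: the attribution of the few gravest events, and the decision on continuing the study that comes straight after it.

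A separate wording problem sits in the same sentence. The trigger is a *severe* event, but the event whose cause is judged is a *serious* one, and grade 3 merges severe with medically significant. Severity is a matter of intensity and seriousness a matter of consequence, so it is unclear which events lead to stopping treatment and opening the code.

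**Working it through.** The point is procedural and rests on the order of steps. Arithmetic serves only to show its scale.

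**1. Order of steps.** The unblinding clause gives its own purpose: the code is broken *to determine* relatedness. Unblinding therefore precedes the centre's verdict. The article describes no blinded verdict before it.

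**2. What the step can and cannot reach.**

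| Item | Depends on the relatedness verdict? | Reason in the protocol |
|---|---|---|
| Count of all adverse events by arm | No | All events are recorded, and all are analysed at the end |
| Primary outcome (area under the pain score curve) | No | Assessors, analysts and statistician stay blinded; nothing says the code reaches them |
| Attribution of severe or serious events | Yes | Verdict formed with the code open |
| Decision on continuing the study | Possibly | Follows the verdict directly; the article does not say who takes it or on what basis |

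**3. Trial size.** The Sample size section gives 12 (read here as per arm) and 20% dropout: 12 / (1 − 0.20) = 15 per arm, and 2 × 15 = 30. The stated size is reproduced.

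**4. Expected number of triggering events.** The documents give no rate, so a range is assumed. Expected number = 30 × p:

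- p = 1%: 30 × 0.01 = 0.3
- p = 2%: 30 × 0.02 = 0.6
- p = 5%: 30 × 0.05 = 1.5
- p = 10%: 30 × 0.10 = 3.0

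**5. How arm knowledge could distort attribution (illustration, all values assumed).** Take an equal true risk of 5% in both arms, with events called related with probability 0.6 in EA and 0.3 in sham once the arm is known.

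- All triggering events: 15 × 0.05 = 0.75 in each arm, equal.
- Called related, EA: 0.75 × 0.6 = 0.45.
- Called related, sham: 0.75 × 0.3 = 0.225.
- Ratio: 0.45 / 0.225 = 2.

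The 2:1 ratio comes wholly from the assumed attribution probabilities (0.6 / 0.3) and does not depend on p. If attribution were equal at 0.5 in both arms, the ratio would be 1. In absolute terms the expected difference here is 0.45 − 0.225 = 0.225 of an event.

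**6. Effect of one changed verdict.** If related events were tabulated by arm, moving one event would shift that arm's proportion by 1/15 = 6.7 percentage points. The article defines no such table, so this shows sensitivity only.

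**The case against.** The strongest reply is that no planned comparison is harmed. The protocol neither records nor analyses events by relatedness, and it defines no rate of related events to compare between arms. A reader might infer from the unblinding clause that the whole safety comparison of EA with sham is biased. The documents do not support that, because total counts are collected and analysed regardless of cause.

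A reader might also infer that the trial's blinding is compromised more widely. That is not supported either. The step belongs to the Clinical Research Center and concerns one participant whose study treatment has already been stopped. Nothing says that the code is passed to the principal investigator, outcome assessors, analysts or statistician.

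A third reply is that a journal article condenses the full protocol. The case report form may already hold a blinded opinion on cause, so it would go too far to say that relatedness is judged only after unblinding. This stands in part: silence about an earlier blinded entry proves little. But the clause on the centre's own determination is a stated rule and not a gap, and that rule uses the code.

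Finally, one may say that with so few events no inference on related severe events is realistic, blinded or not. That is true. It limits the importance of the point, but an opinion on cause for each such event will still be formed and may still be acted on.

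**Conclusion.** The point holds in narrow form and is minor. As written, the centre's verdict on whether a severe or serious event is related to treatment is formed with the arm known. That can influence the attribution of these few events and the decision on continuing the study that follows. Counts of all adverse events and the primary outcome are not affected by this route.

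The size cannot be estimated from the documents. Under assumed risks of 1% to 10%, between 0.3 and 3 events among 30 participants would go through the step, and the degree of distortion depends on attribution probabilities that are also assumed. The conclusion itself needs none of these numbers: it rests on the purpose stated in the unblinding clause and on the difference between the two interventions.

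The mixed use of *severe* and *serious* is a separate, genuine inconsistency. It does not add to the argument about bias, but it leaves the scope of the procedure unclear.

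**What to change.** 1. Before the code is opened, have someone still blinded enter severity, seriousness and relatedness to *study treatment*, without naming an arm, in the case report form. The treating acupuncturist knows the allocation and so cannot be that person.
2. Keep any opinion formed after unblinding as a separate, dated entry.
3. Wherever related events are reported by arm, use the blinded judgement. Continue to report all events regardless of relatedness.
4. Reconcile *severe*, *serious* and the grade 3 wording, so that one defined term states which events enter the procedure. Which events those should be is for the investigators to settle.

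The cost is about two sentences in the protocol, one form field and one extra step before the code is opened. Urgent unblinding for a participant's care is unchanged.
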